After oral intake, DMF is rapidly hydrolyzed by esterases to its active circulating metabolite monomethyl fumarate (MMF). DMF is currently administered due to its lower incidence of gastrointestinal side effects compared to MMF (Litjens et al., 2004). MMF's bioavailability is decreased by concurrent food ingestion, though it remains bioavailable. MMF is the most bioactive metabolite (Litjens et al., 2004) and typically reaches peak serum concentrations around 20 μM. MMF is eliminated mainly through breathing; only small amounts of intact MMF are excreted through urine or feces. There is no evidence for a cytochrome P450-dependent metabolism in the liver, thus few drug interactions would be expected. MMF's half-life *in vivo* is around 12 h. The safety profile of DMF (trade name: Skilarence) is well-known and adverse events of special interest that have been considered for Skilarence are (EMA/412737/2017, 2017) leukocytopenia and lymphopenia, flushing, gastrointestinal disorders, hepatic injury, malignancies, renal injuries and proteinuria, and serious and opportunistic infections. The reported incidence of leukocytopenia is 13.3%, and lymphopenia is 10.0%, with very few patients (<1%) experiencing severe enough lymphopenia (<0.5/L) to lead to discontinuation. Flushing has an incidence of up to 20.8% of patients, is more frequent during the first weeks of treatment, and tends to resolve during long-term administration of DMF. Gastrointestinal disorders were reported in 62.7% of patients receiving DMF. They usually resolved after the first few months of treatment. The proportion of patients with an increase in hepatic enzymes is 7.5% and all are usually mild/moderate intensity. There is no evidence that long-term treatment with DMF is associated with an increased risk of malignancies. The proportion of patients reporting renal injury/proteinuria is low (<3%). Several of these cases of renal toxicity occurred with doses of fumaric acid esters that are much higher than the dose recommended for DMF in psoriasis/MS. In all of these cases, the renal function returned to normal after stopping treatment. The number of infections during DMF treatment was very low (<5%). All infections resolved by the end of the studies or during the 2-month follow-up period. No relation was found between leukopenia/lymphopenia and infections.

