#### Secondary endpoints

The secondary clinical objectives are to examine changes on the cardiopulmonary exercise outputs (VO_2_max, anaerobic threshold, and peak workload) and echocardiographic measures; and to evaluate differences in the Scale for the Rating and assessment of Ataxia (SARA), modified Friedreich Ataxia Rating Scale (m-FARS), 9-hole pegboard test (9HPT), EQ-5D, Activities of Daily Living (ADL)/Instrumental Activities of Daily Living Scale (IADL), and number and distribution of serious and non-serious adverse events between DMF and placebo.

The secondary laboratory objectives are to determine the effect of DMF on *FXN* and frataxin protein considering the change from baseline to week 12 and week 24 and at week 1 of the core phase, and at week 1 of the extension phase for those patients transitioning from placebo to DMF, compared to other time-points obtained after a DMF dose of 240 mg BID. Other secondary endpoints explore the effect of DMF on Nrf2 pathway genes (*NFE2L2, NQO1, HMOX1, PDLIM1*, and *NCF2*), on mitochondrial biogenesis genes (mt-ND6, mtCYB, mt-CO_2_, and mt-ATP6), and on mtDNA/nDNA.

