### Statistical analysis

All data will be preliminary tested for normality using the Kolmogorov–Smirnov test. Since quantitative real time PCR (qPCR) data are frequently not normal, a normalization attempt, using ln or log transformation, will be performed. qPCR data will be calculated as relative increases imputing a baseline expression level of 1.0. Main statistical analysis of both FXN expression and frataxin protein level will be conducted with a Generalized Linear Model (GLM) for repeated measures. GLM incorporates a two-way ANOVA for repeated measures and can accommodate a multivariate analysis of factors and covariates. Treatment with DMF or placebo will be considered as a factor, and baseline levels of frataxin will be considered as a covariate. FXN baseline expression will not be used in the model as it is already integrated using relative expression with common baseline. All other available data (sex, age, disease duration, GAA1, and treatment specific findings, etc.) will be preliminarily tested one by one as covariates. In case of resulting *p*-values < 0.1, they will be integrated in the final multivariate model with treatment as a factor. In case of a significant Maulchy's sphericity test, we will use the Greenhouse-Geisser correction. We will use a similar analysis approach for remaining secondary endpoints. This will include different time-points from FXN and frataxin, and other qPCR analysis, SARA, 9HPT, PRT, ADL/IADL, and EQ-5DVAS. The main analysis will be conducted with results from the core phase of the trial (20 patients treated with DMF and 20 with placebo) and will be used to draw conclusions on the efficacy of DMF. A secondary analysis will be conducted adding to the model patients from the extension phase that switched from placebo to DMF (total of 40 DMF vs. 20 placebo). This analysis will be considered as descriptive and not used to drive efficacy conclusions. For adverse events (AEs), we will perform a descriptive analysis of AEs including their distribution in DMF and placebo treated patients, AEs duration, severity, and connection to the study drug. To test if treatment with DMF increases the likelihood of having an AE, we will use a Generalized Linear Model with Poisson distribution and treatment as a factor. To test if a single AE is more frequently linked to DMF treatment, we will use the exact test of Goodness of fit, assuming an equal proportion of adverse events in the treatment and placebo group. This will be possible only for adverse events occurring at least once in both groups. For baseline variables a descriptive analysis will be performed, and difference between DMF and placebo patients will be tested with an unpaired *t*-test and chi-square test, depending on the variable. In case of non-normal distribution, a Mann–Whitney test will be used in place of a *t*-test. A two-sided significance level of 5% will be required to reject the null hypothesis that the outcome measures are the same before and after treatment, and for all other comparisons. The Bonferroni correction for multiple analyses will be used. Considering the primary endpoint and the phase of the trial, the analysis will be per protocol. Data will be analyzed using the SPSS 23 for MAC (IBM, Chicago, USA).

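### The overall adverse-event test names a Poisson model with no allowance for dispersion and does not define its outcome; it is anti-conservative for AE counts that vary between patients and strongly conservative for any AE yes/no

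*Protocol article*

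**What the plan says.** The Secondary endpoints section lists "number and distribution of serious and non-serious adverse events between DMF and placebo" among the secondary clinical objectives. The Statistical analysis section first promises a descriptive account of AEs by arm, duration, severity and relation to study drug. It then sets one inferential test of AEs overall: "To test if treatment with DMF increases the likelihood of having an AE, we will use a Generalized Linear Model with Poisson distribution and treatment" (the factor in the model). A separate exact test is planned for individual AEs and is not at issue here.

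The same section sets the level: "A two-sided significance level of 5% will be required to reject the null hypothesis", extended to all other comparisons. It adds "The Bonferroni correction for multiple analyses will be used" without giving the number of tests. The core phase compares "20 patients treated with DMF and 20 with placebo".

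The AE sentence mentions no estimated scale, robust variance or negative binomial alternative, and no term besides treatment. It does not define the outcome. No expected AE count per patient, placebo AE rate or between-patient variance appears anywhere in the article.

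**The concern.** A Poisson model with treatment alone takes its standard error from the assumption that, within an arm, the variance of the patient outcomes equals their mean. For AE counts this holds when patients in an arm share one rate and events within a patient are independent. The trial admits patients from age 12 upward, and AEs are recorded at every visit from baseline, so one patient can contribute several related events. If some patients report many AEs and others few, the standard error is too small. The test can then reach significance because patients differ from one another, not because the arms differ.

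The question as worded, about the likelihood of having an AE, also fits a yes/no outcome. There the variance is below the mean, the Poisson standard error is too large, and the test loses power to show a true excess of patients with AEs.

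At stake are the p-value and interval of the only formal comparison of overall AE burden in a 40-patient trial.

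**Working it through.** The plan gives no figure for this test, so there is nothing of its own to reproduce.

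**Inputs from the article:** 20 patients per arm, 1:1 allocation, two-sided 5%, Poisson model with treatment as factor.

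**Assumptions, because the article gives no values:** mean AEs per patient of 0.5 to 4; patient rates gamma-distributed with coefficient of variation (CV) 0.5 to 1.0, with CV 0 as reference; equal exposure; no DMF effect; model-based standard errors with scale fixed at 1.

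**Count outcome.** With arm totals A and B, the test is z = ln(A/B) / √(1/A + 1/B), rejecting at |z| > 1.96. Under varying rates the variance/mean ratio is φ = 1 + mean × CV². The actual type I error is approximately 2 × [1 − Φ(1.96/√φ)].

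- Mean 2, CV 0.5: φ = 1 + 2 × 0.25 = 1.5; 1.96/√1.5 = 1.60; error 11.0%.
- Mean 2, CV 1.0: φ = 3; 1.96/√3 = 1.13; error 25.8%.
- The error reaches 10%, twice nominal, at φ = 1.42.

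Simulated type I error of the Wald test:

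| Mean AEs per patient | CV 0 | CV 0.5 | CV 0.7 | CV 1.0 |
|---|---|---|---|---|
| 0.5 | 4.0% | 5.4% | 6.7% | 9.2% |
| 1 | 4.5% | 7.4% | 10.1% | 15.3% |
| 2 | 4.8% | 10.6% | 15.6% | 25.1% |
| 4 | 4.8% | 16.0% | 25.3% | 37.8% |

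Where the likelihood-ratio test was also run (means 0.5, 1 and 2), it was within about 2 percentage points of these values. With the scale estimated from the Pearson chi-square and a t reference on 38 df, the error is 4.5-5.2% for means of 1 to 3 and CV 0.5-1.0, and about 4% at mean 0.5.

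A hypothetical result shows the effect. With 60 AEs on DMF and 40 on placebo, z = ln(1.5)/√(1/60 + 1/40) = 0.405/0.204 = 1.99, which is significant at 5%. With φ = 2 the statistic becomes 1.99/√2 = 1.40, which is not.

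**Bonferroni.** If ten tests are assumed, the nominal level is 0.05/10 = 0.5%. The same formula, with 2.81 in place of 1.96, gives 4.7% at φ = 2 and 10.5% at φ = 3. That is about 9 and 21 times nominal, against 16.6/5 = 3.3 and 25.8/5 = 5.2 times at the uncorrected 5% level. The absolute rates fall; the relative inflation does not.

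**Yes/no outcome.** For incidence p the variance is p(1 − p) and the mean is p, so the ratio is 1 − p, below 1. The simulated error is 0.8% at p = 40%, 0.19% at 60% and 0.13% at 62.7%. The last value borrows the article's statement that "Gastrointestinal disorders were reported in 62.7% of patients receiving DMF", purely as an example of a plausible incidence.

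As a hypothetical case, take 16 of 20 patients with an AE on DMF and 8 of 20 on placebo. The Poisson statistic is ln(2)/√(1/16 + 1/8) = 0.693/0.433 = 1.60, not significant. An ordinary comparison of proportions gives (0.8 − 0.4)/√(0.6 × 0.4 × 2/20) = 0.4/0.155 = 2.58.

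**The case against.** A reader might infer that the planned test is bound to reject far above 5% when DMF has no effect. The article does not support that, for these reasons:

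- **The outcome is open.** The count reading is the more natural one for a Poisson model, but the wording also allows yes/no, and then the error runs the other way.
- **The size rests on assumptions.** At 0.5 to 1 AE per patient and CV 0.5, the error is only about 5-7%. The 62.7% figure for gastrointestinal disorders is a proportion of patients from the drug's known safety profile; it says nothing about counts or their spread in this trial.
- **The null is equal mean rates in the two arms.** A common rate across patients is a variance assumption behind the standard error. It is not part of the null.
- **Bonferroni applies.** Absolute error rates calculated at an uncorrected 5% need not be those of the final test.

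All four limits stand. Two further arguments have less force. The first is that scale and variance options belong in an analysis plan that is not shown, and that a Pearson-scaled model is still a Poisson GLM. But the article does more than stay silent: it names a distribution and a factor, and read plainly that fixes variance equal to mean. The second is that safety will mainly be judged descriptively. That limits the consequence but leaves the formal test miscalibrated.

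**Conclusion.** The point holds in conditional form. As written, the overall AE test has its nominal level only in the special case of a count outcome with variance equal to mean within each arm. For counts with an assumed CV of 0.5-1.0 and 20 per arm, type I error is about 5-9% at 0.5 AE per patient and 16-38% at 4, before Bonferroni. For any AE yes/no it is below 1% at 40-63% incidence. The direction therefore depends on an outcome that the article does not define, and the size depends on AE rates and spread that it does not give. This concerns one secondary safety test. It should be corrected, but it does not touch the primary endpoint or the sample size.

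**What to change.** Replace the overall AE sentence in the Statistical analysis section with text that does three things:

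1. State the outcome, and which comparison is the formal test if both outcomes below are reported.
2. For the number of AEs per patient, use a log-link Poisson model with the dispersion estimated from the Pearson chi-square (quasi-Poisson) and a t reference on N − 2 df (38 with 40 patients). Report the rate ratio with its 95% confidence interval.
3. For the proportion of patients with at least one AE, report the risk difference with an exact 95% confidence interval in place of the Poisson model.

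The cost is a short change of text and a model option in the software, with no new data or patients. The interval for the rate ratio widens on the log scale by about √φ, for example √2 = 1.41 times at a variance/mean ratio of 2, and nominal significance becomes harder to reach. That width reflects the uncertainty actually present.

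### The single-adverse-event test excludes events seen in only one arm, so the most extreme imbalances against DMF get no test

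*Protocol article*

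**What the plan says.** The Secondary endpoints section of the protocol article includes the "number and distribution of serious and non-serious adverse events between DMF and placebo". The Statistical analysis section then sets out three layers of analysis for adverse events:

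- **Description.** "we will perform a descriptive analysis of AEs including their distribution in DMF and placebo treated patients", together with duration, severity and relation to study drug.
- **Overall test.** For whether DMF raises the likelihood of an adverse event, "we will use a Generalized Linear Model with Poisson distribution and treatment as a factor".
- **Single-event test.** "To test if a single AE is more frequently linked to DMF treatment, we will use the exact test of Goodness of fit". The null hypothesis is an even split of events, not of patients, between the arms. The next sentence restricts it: "This will be possible only for adverse events occurring at least once in both groups".

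The main analysis has 20 patients per arm, at a two-sided 5% level. A Bonferroni correction for multiple analyses is announced, but the article does not say whether it covers the adverse event tests.

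**The concern.** The restriction is presented as a matter of feasibility, and that premise is false. An exact test of a 50:50 split can be computed for any pair of counts with a positive total, including a zero.

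The effect runs the wrong way. Whether an event is tested depends on its outcome, and the events removed include the most one-sided ones. A drug that causes an event rarely seen on placebo is likely to produce just that pattern in arms of 20. A report could then state that no single event differed significantly between arms when the clearest differences had not been eligible for testing.

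A second, conditional weakness lies in the unit. The null hypothesis is stated for events, and the test uses no patient denominators. If several episodes in one patient are counted separately, the test treats them as independent observations.

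**Working it through.** The plan gives no figure for these tests, so there is none to reproduce.

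**Inputs**
- 20 patients per arm in the core phase, two-sided 5% (Statistical analysis).
- DMF incidences: flushing up to 20.8%, gastrointestinal disorders 62.7% (section on the drug). They are applied here as per-patient risks over the core phase.
- Placebo incidences are not given. A range of 0 to 10% is assumed.
- Steps 1 to 3 count each patient once per event. No Bonferroni correction is applied to any p-value.

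**Step 1: is the test defined with a zero?** For a split of x to 0, the exact two-sided p-value against 50:50 is 2 × 0.5^x.
- 6 to 0: 2/64 = 0.031
- 8 to 0: 2/256 = 0.0078
- 8 to 1: 2 × (1 + 9)/512 = 0.039

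The plan tests the last and excludes the first two. Fisher's exact test on patients gives:
- 6/20 vs 0/20: p = 0.020
- 8/20 vs 0/20: 2 × C(20,8)/C(40,8) = 2 × 125,970/76,904,685 = 0.0033

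**Step 2: how often would flushing be excluded?** With placebo risk q, the chance of at least one DMF case and no placebo case is [1 − (1 − 0.208)^20] × (1 − q)^20. The first factor is 1 − 0.0094 = 0.991. The last three columns give the chance of p ≤ 0.05, from exact enumeration of both binomial counts.

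| Assumed placebo risk | DMF only, untested | Planned test, restricted | Same test, unrestricted | Fisher on patients |
|---|---|---|---|---|
| 0% | 99% | 0% | 22% | 40% |
| 1% | 81% | 0.7% | 19% | 35% |
| 2% | 66% | 1.1% | 16% | 30% |
| 5% | 36% | 1.6% | 10% | 19% |
| 10% | 12% | 1.2% | 4% | 8% |

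**Step 3: is the loss due to the restriction or to the sample size?** Gastrointestinal events separate the two, because at 62.7% there is ample power. At an assumed placebo risk of 2%, the unrestricted goodness-of-fit test is significant with probability 99.0% and the restricted one with 32.3%. The difference, 66.7 percentage points, is the probability of six or more DMF cases with no placebo case: the significant results that the rule discards. Fisher's test gives 99.7%.

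**Step 4: repeat episodes, only if counted separately.** This is a simulation of 20,000 trials with no treatment effect. It assumes that 20% of patients in each arm have the event and that each of them has on average 1, 2 or 4 further episodes. The event-count test without the restriction rejects in 13, 23 and 35% at the nominal 5%. Fisher's test on patients rejects in about 2%.

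**The case against.** **The events are not hidden.** Events seen only on DMF enter the descriptive analysis and the overall Poisson model, so a 6 to 0 split would be visible in the tables. This stands. It would be too strong to infer that they are never analysed; what they lack is the single-event test. The overall model cannot fill that gap, because it does not show which event is raised.

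**Repeat counting is a reading.** The article nowhere says that episodes within a patient are counted separately, and its phrase about the likelihood of having an adverse event also fits one count per patient. This stands too. The event wording and the absence of denominators make separate counting the natural reading, but if each patient counts once, step 4 falls away. Steps 1 to 3 do not depend on it.

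**Multiplicity and sample size.** If Bonferroni covers even three event types (0.05/3 = 0.0167), the 6 to 0 and 8 to 1 examples are no longer significant; 8 to 0 still is. At 20.8%, eight or more flushing cases among 20 has a chance of only about 4%. Lymphopenia at the protocol's 10.0% would rarely reach significance under any test: with no placebo cases, Fisher's test needs five DMF cases, a 4.3% chance. The gain for such events is mainly an estimate with an interval. These limits are real, but they do not justify a rule that tests 8 to 1 and omits 8 to 0.

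**Inferences the document does not support.** A reader might conclude that the Poisson model is misspecified because no exposure offset or overdispersion term is named. A condensed article can leave that to the analysis plan. A reader might also suppose that extension-phase events are pooled with core-phase events. The comparison of 40 DMF with 20 placebo patients is described as a secondary analysis after the main efficacy analysis and is not linked to adverse events.

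**Conclusion.** The restriction is wrong as written. It rests on a false premise and removes the most extreme splits from the single-event test. For flushing at 20.8% on DMF, the chance of going untested ranges from 99% to 12% as the assumed placebo risk goes from 0 to 10%. For gastrointestinal events at 62.7% and an assumed placebo risk of 2%, the chance of a significant result falls from 99% to 32%. Both results rest on the assumed placebo risks, on the protocol's DMF incidences applying over 12 weeks, on one count per patient, and on no Bonferroni correction.

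The dependence between repeat episodes is a conditional addition to this. Severity is moderate to minor: the analysis is of secondary safety data, and neither the primary endpoint nor data collection is affected.

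**What to change.** - Delete the sentence "This will be possible only for adverse events occurring at least once in both groups".
- For each adverse event, compare between arms the number of patients with at least one event in the core phase, using Fisher's exact test. Report the risk difference with an exact confidence interval.
- State that the patient is the counting unit for this comparison, and describe repeat episodes by arm.

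This is a change of wording, best made before unblinding. The data are already to be collected, and no further patients or visits are needed. The small cost is that repeat episodes are then only described, not tested.

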We performed an exploratory study to limit expenses and risks related to a straight phase II trial with DMF in patients with FRDA. We enrolled multiple sclerosis (MS) patients, for which a decision to start a therapy with DMF (*n* = 14) had already been taken as part of normal clinical practice, at the standard dose of 240 mg BID. We added to this study a parallel group of patients that started a treatment with fingolimod (*n* = 12), a recently approved oral treatment for MS, that served as a control group. We also enrolled twelve healthy controls. Baseline levels of FXN/mRNA in PBMCs were similar between controls and MS patients (*p* = 0.818). After 3 months of treatment, FXN/mRNA expression increased by 85.1% in the DMF group and 13.7% in the fingolimod group (relative increase in DMF +71.4%; *p* = 0.011). DMF also caused a 70% increase in mitochondrial copy number in PBMCs and an >100% increase in mitochondrial complex subunit expression of mt-ND6 (complex 1), mt-CYB (complex 3), mt-CO_2_ (complex 4) and mt-ATP6 (complex 5). The increase in these four transcripts could result in an *in-vivo* stimulation of mitochondrial biogenesis and improvement of oxidative phosphorylation, known to be impaired in FRDA patients (Hayashi et al., 2017).

Since MS patients showed comparable basal levels of FXN/mRNA to healthy controls, it is possible that DMF can increase FXN/ mRNA levels in healthy individuals as well as in patients with MS.

Based on the previous points, the aim of our study is to further investigate the role of DMF in FRDA and to demonstrate if DMF is able to correct the biological deficits of FRDA. The study will contribute to the understanding of the ability *in-vivo* of DMF, at currently approved doses for MS and psoriasis, to increase the expression of the *FXN* gene and to increase frataxin protein.

We propose a double-blind, placebo-controlled, randomized, phase II clinical trial to test the effect of DMF on FXN transcription in FRDA patients. The secondary objectives of the study will be the effect of DMF on frataxin protein, the nrf2 pathway, and mitochondrial biogenesis, safety and tolerability, and clinical aspects of the disease.

We hypothesize that DMF is superior to placebo in its ability to increase FXN/mRNA.

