**Figure 2 F2:**
[figure not shown]
Study visit plan and procedures. V1, visit 1; V2, visit 2; V3, visit 3; V4, visit 4; V5, visit 5; V6, visit 6; V7, visit 7; V8, visit 8; V9, visit 9; V10, visit 10; ECG, electrocardiogram; Con Meds, concomitant medications; SARA, Scale for the Rating and Assessment of Ataxia; m-FARS, modified Friedreich Ataxia Rating Scale; FXN/mRNA, *FXN* gene mRNA measurement; PRT, PATA rate test; 9HPT, 9 hole pegboard test; ADL/IADL, activities of daily living/Instrumental activities of daily living; EQ-5D, European quality of life scale; CPET, cardiopulmonary exercise test; EcoCG, echocardiography.

The use of placebo is based on several factors. On one side, there is a need for a more accurate evaluation on the biochemical effect on FXN/mRNA and frataxin that can show fluctuations over time. For this reason, an increase of FXN/mRNA in an open-label trial could be erroneously attributed to treatment. The second reason is that secondary endpoints (CPET, Clinical scales, etc.) can show a clear placebo effect once patients take part in a clinical trial. There is no known risk of being in the placebo group as there is no treatment available for FRDA.

The study will begin with a screening visit where patients will sign their informed consent (Figure 2). We will then assess inclusion and exclusion criteria (Table 1). Patients fulfilling all inclusion and none of the exclusion criteria will undergo endpoint measurement and will enter the core phase of the study.

**Table 1 T1:** Inclusion and exclusion criteria.

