### Endpoints

#### Primary endpoints

The primary objective of the study is to evaluate the effect of DMF compared to placebo on *FXN* gene expression level considering the change from baseline to 12 weeks (core phase of the DMF-FA-201 study).

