### Sample size calculation

Sample size calculation was performed based on our preliminary results of DMF treatment in patients with Multiple Sclerosis and is based on the estimated increase in FXN expression with the following assumptions derived from our preliminary data (Jasoliya et al., 2019). We previously found a significant +85% increase in the group treated with DMF compared to no increase in the control group (time^*^treatment interaction *p* = 0.02), which resulted in a partial eta square of 0.198. The sample size in this study was 14 patients treated with DMF and 13 with reference control treatment. The partial eta square of 0.198 results in an effect size of 0.497. Estimating the effect size based on preliminary data on MS patients is an underestimation of the potential effect of DMF in FRDA patients. Indeed, DMF can overexpress FXN through two mechanisms. One is the stimulation of nrf2 and the increase in transcription of several genes, including antioxidant genes and frataxin. This mechanism is clearly involved in MS patients treated with DMF. The second mechanism is the ability of DMF to induce transcription initiation and reduce transcriptional pausing in mutant *FXN* gene. This mechanism is unique to FRDA patients as it requires a mutated gene to be effective. In support of this, experiments in patients' lymphoblasts treated with DMF have found up to a +260% increase relative to baseline (Lynch et al., 2010), compared to our finding of +85% increase in MS patients treated with DMF. Based on this data, we calculated the appropriate sample size for this study using G^*^Power version 3.1.9.6. We used an ANOVA for repeated measures, within-between interaction, as the appropriate test. Effect size was set at 0.497, alpha error at 0.05, power at 0.8, number of groups 2, number of measurements 2, and non-sphericity correction 1. This results in a total population of 36 patients (18 treated + 18 placebo). We will prudently include 40 patients in total, allowing us to compensate for a lost at follow-up of up to 10% of randomized patients.

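### The stated null hypothesis is a before-after one, although the trial asks and is powered for DMF versus placebo; the deciding model term and the primary test's place outside Bonferroni should be stated

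*Protocol article*

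**What the plan says.** All of the following is from the Protocol article.

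- **Statistical analysis, decision rule:** a two-sided 5% level is needed to "reject the null hypothesis that the outcome measures are the same before and after treatment", continuing "and for all other comparisons". The next sentence is "The Bonferroni correction for multiple analyses will be used". It names no family or divisor and does not mention the primary test.
- **Statistical analysis, model:** FXN expression and frataxin protein are both placed under the main analysis, a repeated-measures general linear model with treatment (DMF or placebo) as a factor. Efficacy conclusions come from the core phase, 20 patients per arm.
- **Study rationale:** "We hypothesize that DMF is superior to placebo in its ability to increase FXN/mRNA".
- **Primary endpoints:** the objective is to "evaluate the effect of DMF compared to placebo on" FXN expression, as change from baseline to 12 weeks.
- **Trial design and intervention (paragraph after Figure 2):** placebo is used because FXN/mRNA can fluctuate over time, so that "an increase of FXN/mRNA in an open-label trial could be erroneously attributed to treatment".
- **Sample size calculation:** the powered test is the within-between interaction of a repeated-measures ANOVA with two groups and two measurements. "Effect size was set at 0.497, alpha error at 0.05, power at 0.8". The result is 36 patients, raised to 40 for 10% loss.

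**The concern.** A repeated-measures model with a treatment factor yields three tests: time, treatment, and treatment by time. The time test asks whether patients changed, whatever they received. The interaction asks whether they changed by different amounts under DMF and placebo. The trial was designed to answer the second question. The only null the protocol writes down describes the first, and no sentence names the deciding term.

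This matters because the protocol itself expects FXN/mRNA to fluctuate. A rise common to both arms, from the assay, from season or from taking part in a trial, would reject a before-after null and say nothing about DMF. That is the error the placebo arm was added to prevent.

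A smaller point belongs with it. The sample size spends the whole 0.05 on one primary test, while the Bonferroni sentence does not say that this test is exempt.

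**Working it through.** **1. The plan's own sample size.** Inputs from the Sample size calculation: partial eta squared 0.198, alpha 0.05, power 0.80, two groups, two measurements, non-sphericity correction 1.

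- Effect size: f = √(0.198 / 0.802) = 0.497, as stated.
- Interaction test: F with 1 and N − 2 degrees of freedom and noncentrality λ = f²(N − 2).
- At N = 36: λ = 0.247 × 34 = 8.40, critical F(1, 34) = 4.13, power 0.804. At N = 34 the power is 0.778, so 36 is the smallest even total that reaches 80%.
- Loss: 36 / 0.90 = 40. If all 40 are analysed, power is 0.847.

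The stated 36 and 40 reproduce, and they reproduce for the between-group test. The sample size already addresses DMF versus placebo.

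**2. The passages side by side.**

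| Place | Comparison described |
|---|---|
| Study rationale | DMF against placebo |
| Primary endpoints | DMF against placebo, change to week 12 |
| Trial design and intervention | a rise without a control is not evidence of effect |
| Sample size calculation | treatment-by-time interaction |
| Statistical analysis, model | treatment as a factor; deciding term not named |
| Statistical analysis, null hypothesis | before against after |

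The last row stands alone.

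**3. What a literal time test would do.** Assume an inert drug and a drift δ common to both arms, in units of the SD of the change score. The protocol gives no value, so a range is shown. The time test at N = 36 has λ = 36 δ² on 1 and 34 degrees of freedom, with critical F = 4.13 (t = 2.03).

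| Common drift δ | λ | Chance of rejecting the before-after null |
|---|---|---|
| 0.2 SD | 1.44 | 0.21 |
| 0.3 SD | 3.24 | 0.42 |
| 0.5 SD | 9.00 | 0.83 |

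The interaction test would reject in 5% of such trials whatever the drift, because a shared drift cancels between arms.

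**4. Bonferroni, if it reached the primary.** The protocol gives no divisor. The largest its wording suggests is k = 2, because FXN expression and frataxin protein share one main analysis. At alpha 0.05 / 2 = 0.025, with the formula of step 1:

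| Analysed | k = 1 | k = 2 |
|---|---|---|
| 36 | 0.80 | 0.71 |
| 40 | 0.85 | 0.76 |

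If Bonferroni covers only the other analyses, the k = 1 column applies.

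**The case against.** The strongest reply is that the document, read as a whole, leaves no doubt about the comparison. The hypothesis, objective and powered test are all between groups, the model contains treatment, efficacy is to be judged from 20 against 20 patients, and the sentence with the wrong null extends the 5% level to all other comparisons. This stands so far as intent goes. A reader might infer that the trial's primary decision rule as a whole is a before-after test; the documents do not support that. It does not remove the point. The one sentence that defines what must be rejected names the wrong hypothesis, and the right one has to be pieced together from other sections.

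The 83% figure can be challenged because 0.5 SD is an assumption and the protocol never names the pooled time effect as its efficacy test. Both are correct. The table illustrates a literal reading and does not estimate this trial's error rate.

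On Bonferroni, a 5% overall level that the correction then protects is coherent. With one primary endpoint, the usual reading is that it keeps 0.05. The family and divisor for the other analyses are commonly left to the full protocol or SAP, which are not shown, so their absence is no finding. A reader might infer that the correction removes most of the planned power. At N = 36 power falls below half of 0.80 only near k = 20 (0.38), and nothing in the text puts the single primary test in a family of that size.

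**Conclusion.** The point holds as an error in the stated null hypothesis. It contradicts four other places in the same document, and the Statistical analysis section does not name the model term that settles the primary question. This part does not depend on any assumption.

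Its numerical size does. For an inert drug and a shared drift of 0.2 to 0.5 SD of the change, a literal time test at N = 36 would reject in about 21% to 83% of trials, against a nominal 5%.

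The Bonferroni part is a clarification. A loss of power arises only if the primary test is inside the corrected family: at k = 2, to 0.71 with 36 patients and 0.76 with 40. The documents do not show that it is. They also give no ground for calling the sample size wrong: 36 reproduces at power 0.804, and correcting the null changes neither it nor the 40 enrolled.

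**What to change.** Make these changes before unblinding:

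1. Restate the null as: no difference between DMF and placebo in the change of FXN expression from baseline to week 12. Name the treatment-by-time interaction, on the two measurements used in the sample size calculation, as the deciding term, tested once at two-sided 0.05. Describe within-arm before-after tests as descriptive only.
2. State that the Bonferroni correction excludes this single primary test, as the sample size at alpha 0.05 assumes. If frataxin protein is meant to be a joint main outcome, say so and recalculate the sample size at the adjusted level.

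The cost is two or three sentences. With the primary test kept at 0.05, no patients, visits or data are added, and the model and the sample size stay as they are.
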